### [^18^F]-FDG PET

Data-analysis will be done using in-house developed software, including SUV_max_, SUV_peak_, 70% VOI, 50% VOI, normalized for serum glucose and body weight. Metabolic tumor volume (MTV is defined with an isocontour VOI of 50% of SUV_peak_ with background correction) and total lesion glycolysis (TLG is defined as SUV_mean corrected for body weight_ times MTV). Early response will be categorized according to PERCIST [67].

## Nivolumab treatment

Patients will be treated with a single flat dose of 480 mg nivolumab IV. The infusion protocol can be found in the investigator brochure [32]. There are no pre-medications recommended for nivolumab. There will be no dose modifications allowed. Subjects will be carefully monitored for infusion reactions during nivolumab administration. If an acute infusion reaction is noted, subjects will be managed according to protocol Section 5.2.6.

### Nivolumab preparation, handling and dispensing

Preparation and administration of Nivolumab

1. Visually inspect the drug product solution for particulate matter and discoloration prior to administration. Discard if solution is cloudy, if there is pronounced discoloration (solution may have a pale-yellow color), or if there is foreign particulate matter other than a few translucent-to-white, amorphous particles.

*Note: Mix by gently inverting several times. Do not shake.*

1. Aseptically withdraw the required volume of nivolumab solution into a syringe, and dispense into an IV bag. If multiple vials are needed for a subject, it is important to use a separate sterile syringe and needle for each vial to prevent problems such as dulling of needle tip, stopper coring, repeated friction of plunger against syringe barrel wall. Do not enter into each vial more than once. Do not administer study drug as an IV push or bolus injection.
2. Add the appropriate volume of 0.9% Sodium Chloride Injection solution or 5% Dextrose Injection solution. It is acceptable to add nivolumab solution from the vials into an appropriate pre-filled bag of diluent.

*Note: Nivolumab infusion concentration must be at or above the minimum allowable concentration of 0.35 mg/mL. For greater detail, see the Investigator Brochure [32].*

*Note: It is not recommended that so-called “channel” or tube systems are used to transport prepared infusions of nivolumab.*

1. Attach the IV bag containing the nivolumab solution to the infusion set and filter.
2. At the end of the infusion period, flush the line with a sufficient quantity of approved diluents.

Handling and dispensing of nivolumab

The study drug should be stored in accordance with the environmental conditions (temperature, light, and humidity) as per product information and the Investigator Brochure and per local regulations [32]. It is the responsibility of the investigator to ensure that investigational product is only dispensed to study subjects. The investigational product must be dispensed only from official study sites by authorized personnel according to local regulations. If concerns regarding the quality or appearance of the study drug arise, the study drug should not be dispensed and contact BMS immediately.

Please see the Investigator Brochure version 13 for additional information on storage, handling, dispensing, and infusion information for nivolumab [32].

### Dose modifications

Dose reductions or dose escalations are not permitted.

### Toxicity management algorithms

Although patients will receive only a single dose of nivolumab, (immune-related) adverse events other than infusion-related reactions may occur. Subjects should receive appropriate supportive care measures as deemed necessary by the treating investigator including but not limited to the items outlined below:

Immuno-oncology (I-O) agents are associated with Adverse Events (AEs) that can differ in severity and duration than AEs caused by other therapeutic classes. Nivolumab is considered an I-O agent in this protocol. Management algorithms have been developed to assist investigators in assessing and managing the following groups of AEs: Gastrointestinal, Renal, Pulmonary, Hepatic, Endocrinopathies, Skin, Neurological. These algorithms concern mainly patients who are continuously treated with nivolumab. Nevertheless, in case immune –related events occur, the management algorithms that have been developed, should be followed. Details can be found in the [Appendix 3](#_APPENDIX_3:_Management).

### Discontinuation criteria

As nivolumab will only be administered once, no discontinuation criteria apply.

### Treatment of nivolumab related infusion reactions

Since nivolumab contains only human immunoglobulin protein sequences, it is unlikely to be immunogenic and induce infusion or hypersensitivity reactions. However, if such a reaction were to occur, it might manifest with fever, chills, rigors, headache, rash, pruritus, arthralgia’s, hypo- or hypertension, bronchospasm, or other symptoms of allergic-like reactions.

All Grade 3 or 4 infusion reactions will be reported as an SAE if criteria are met. Infusion reactions will be graded according to National Cancer Institute (NCI) Common Terminology for Adverse Events (CTCAE) version 5.0 guidelines.

Treatment recommendations are provided below:

For Grade 1 symptoms: (Mild reaction; infusion interruption not indicated; intervention not indicated). Remain at bedside and monitor subject until recovery from symptoms.

For Grade 2 symptoms: (Moderate reaction requires therapy or infusion interruption but responds promptly to symptomatic treatment [e.g., antihistamines, non-steroidal anti-inflammatory drugs, narcotics, corticosteroids, bronchodilators, IV fluids]; prophylactic medications indicated for 24 hours).

Stop the nivolumab infusion, begin an IV infusion of normal saline, and treat the subject with diphenhydramine 50 mg IV (or equivalent) and/or paracetamol 325 to 1000 mg (acetaminophen); remain at bedside and monitor subject until resolution of symptoms. Corticosteroid or bronchodilator therapy may also be administered as appropriate. If the infusion is interrupted, then restart the infusion at 50% of the original infusion rate when symptoms resolve; if no further complications ensue after 30 minutes, the rate may be increased to 100% of the original infusion rate. Monitor subject closely. If symptoms recur then no further nivolumab will be administered at that visit. Administer diphenhydramine 50 mg IV, and remain at bedside and monitor the subject until resolution of symptoms. The amount of study drug infused must be recorded on the electronic case report form (eCRF). The following prophylactic premedications are recommended in case a second infusion the next day seems appropriate (in case < 25% of nivolumab has been administered): diphenhydramine 50 mg (or equivalent) and/or paracetamol 325 to 1000 mg (acetaminophen) should be administered at least 30 minutes before additional nivolumab administrations. If necessary, corticosteroids (recommended dose: up to 25 mg of IV hydrocortisone or equivalent) may be used.

For Grade 3 or Grade 4 symptoms:
Severe reaction, Grade 3: prolonged [ie, not rapidly responsive to symptomatic medication and/or brief interruption of infusion]; recurrence of symptoms following initial improvement; hospitalization indicated for other clinical sequelae [eg, renal impairment, pulmonary infiltrates]).
Grade 4: (life threatening; pressor or ventilatory support indicated). Immediately discontinue infusion of nivolumab. Begin an IV infusion of normal saline, and treat the subject as follows. Recommend bronchodilators, epinephrine 0.2 to 1 mg of a 1:1,000 solution for subcutaneous administration or 0.1 to 0.25 mg of a 1:10,000 solution injected slowly for IV administration, and/or diphenhydramine 50 mg IV with methylprednisolone 100 mg IV (or equivalent), as needed. Subject should be monitored until the investigator is comfortable that the symptoms will not recur. Nivolumab will be permanently discontinued. Investigators should follow their institutional guidelines for the treatment of anaphylaxis. Remain at bedside and monitor subject until recovery from symptoms.

In the case of late-occurring hypersensitivity symptoms (eg, appearance of a localized or generalized pruritus within 1 week after treatment), symptomatic treatment may be given (eg, oral antihistamine, or corticosteroids).

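### Section 5.6.5 handles an infusion reaction that recurs after restart in two ways: the Grade 2 text leaves a next-day infusion open, while the Grade 3/4 text requires permanent discontinuation

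*Protocol*

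**What the plan says.** Protocol Section 5.6.5 sets out management of nivolumab infusion reactions by CTCAE grade.

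- **Grade 2.** The reaction is one that "responds promptly to symptomatic treatment". The infusion is stopped, the patient is treated, and staff then "restart the infusion at 50% of the original infusion rate when symptoms resolve". For a reaction that returns, the instruction is: "If symptoms recur then no further nivolumab will be administered at that visit". Shortly afterwards, premedication is recommended "in case a second infusion the next day seems appropriate (in case < 25% of nivolumab has been administered").
- **Grade 3 or 4.** One heading and one list of actions cover both grades. The Grade 3 description includes "recurrence of symptoms following initial improvement". The actions include immediate discontinuation of the infusion and the statement: "Nivolumab will be permanently discontinued".

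Two nearby sections bear on the point. Section 5.6.4 states: "As nivolumab will only be administered once, no discontinuation criteria apply". Section 5.6 says that for an acute reaction "subjects will be managed according to protocol Section 5.2.6", a number that does not exist in the protocol.

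**The concern.** A reaction that resolves, permits a half-rate restart and then returns fits both parts of Section 5.6.5. Under the Grade 2 part, dosing ends for that visit, and a further infusion the next day remains open at the investigator's discretion if less than a quarter of the dose was given. Under the Grade 3/4 part, the patient receives no more nivolumab. No sentence in the protocol says which part governs.

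The stake is a bedside re-exposure decision. The feasibility and safety of nivolumab before surgery form a primary objective (Section 2.1), and the patients are awaiting curative surgery. A reader of the Grade 2 paragraph alone could re-dose a patient whom the next paragraph bars.

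**Working it through.** The protocol states no figure to reproduce here. The check is a comparison of texts, followed by two small calculations of scale.

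**Tracing one patient through Section 5.6.5**

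| Step | Grade 2 text | Grade 3/4 text |
| --- | --- | --- |
| Symptoms appear and respond promptly to treatment | Stop, treat, restart at half rate | Not engaged |
| Symptoms return after restart | No more nivolumab at this visit | Recurrence after improvement is listed as Grade 3; stop at once |
| Next day, less than 25% given | Second infusion possible if judged appropriate | Barred; discontinuation is permanent |

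The last two rows differ. Three readings that might remove the difference were tried.

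1. *Permanent discontinuation applies to Grade 4 only.* The actions stand under a heading that names both grades. On this reading Grade 3 would have no management instruction.
2. *Recurrence is simply Grade 3, so the Grade 2 text falls away.* The Grade 2 text contains its own recurrence step with a weaker stop, and this reading would leave that step without a use.
3. *The next-day sentence is meant only for reactions without recurrence.* It can be used without conflict for a Grade 2 reaction that resolved but was not restarted that day. The text does not limit it to that case. Because restart is directed once symptoms resolve, recurrence is the main route by which a Grade 2 patient ends the visit with less than 25% given.

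**Dose at issue.** Input: a single flat dose of 480 mg (Section 5.6).

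- Threshold: 0.25 × 480 = 120 mg, so the patient has received less than 120 mg.
- Remainder: 480 − 120 = 360 mg, so more than 360 mg is outstanding. That a next-day infusion would give the remainder is an assumption, since Section 5.6.5 states no amount.

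**How often.** Input: 15 evaluable patients (Section 4.3). The documents give no rate for recurrence after restart with less than 25% infused. Taking p from 0.1% to 1% as an assumption, the chance of at least one case is 1 − (1 − p)^15 and the expected number is 15p:

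| Assumed p | Chance of at least one case in 15 | Expected cases |
| --- | --- | --- |
| 0.1% | 1.5% | 0.015 |
| 0.2% | 3.0% | 0.03 |
| 0.5% | 7.2% | 0.075 |
| 1% | 14.0% | 0.15 |

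These figures count recurrences. Re-exposure also requires an investigator who chooses to re-dose, so its probability is lower.

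**The case against.** A reader might infer that the section issues two incompatible orders, so that whatever the investigator does breaks the protocol. The text does not support that. Section 5.6.5 introduces its guidance as recommendations, and the next-day sentence recommends premedication if a second infusion seems appropriate; it does not order one. Where the Grade 3/4 text requires permanent discontinuation, a second infusion can be judged inappropriate. Stopping therefore complies with every sentence.

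There is also a route to the Grade 3 rule. Reactions are graded by CTCAE, and Section 8.1.1 expects changes of grade within an episode to be recorded. A Grade 2 reaction that returns can be regraded and managed as Grade 3.

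Both arguments stand as far as they go. They show that a careful investigator will reach the safe answer. They do not remove the problem, because the Grade 2 text gives its own, weaker instruction for recurrence, and nothing tells a reader who stops there to go on to the next paragraph.

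Two further points should carry no weight. Section 5.6.4 is ordinary wording for a single-dose regimen; it does not settle the question, but it did not create it. The wrong section number in Section 5.6 is a clerical slip, since the contents list shows only one section on infusion reactions. It should also be said that Section 5.6 places the infusion protocol in the investigator brochure, which is not at hand, so the statement that nothing else sets precedence covers the protocol only.

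**Conclusion.** The inconsistency is real, and as wording for a safety rule it should be corrected. It is minor. Harm requires a Grade 2 reaction, resolution, restart, recurrence before a quarter of the dose is in, and a decision to re-dose despite the Grade 3 text. Section 5.6.5 itself considers infusion reactions unlikely, and the frequency range above rests wholly on an assumed rate.

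A reader might also infer that adverse event grading, serious event reporting or the study results are affected. The documents do not support this. CTCAE sets the grade, Section 5.6.5 reports Grade 3 or 4 reactions as serious only where the criteria are met, and Section 8.1.1 requires every event to be assessed for seriousness whatever its grade. The PET endpoints and their analysis do not depend on the wording.

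**What to change.** In Section 5.6.5:

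1. At the Grade 2 recurrence step, state that symptoms returning after restart are managed as Grade 3 and that nivolumab is permanently discontinued.
2. In the next-day sentence, add to the 25% condition that symptoms did not recur after restart. This keeps the option for Grade 2 reactions without recurrence.

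A separate cap on the total dose is hardly needed, since Section 5.6 fixes a single 480 mg dose and Section 5.6.2 bars escalation. Correcting the reference in Section 5.6 from 5.2.6 to 5.6.5 is tidying that can be done in the same amendment.

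The cost is two sentences of wording, with no new data or visits. The downside is that a patient whose reaction recurs before a quarter of the dose is given stays below 120 mg. Section 7.18.2 names only failed PET scans and proven metastases as grounds for replacement. Section 4.3 asks for 15 evaluable patients without defining the term, so whether such a patient would count is not settled.

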# ENDPOINTS

## Main study parameters/endpoints

PET Imaging

[^18^F]BMS-986192 and [^18^F]-FDG SUV_max_, SUV_mean,_ SUV_peak_ will be measured in all tumor lesions and (enlarged) lymph nodes using manually drawn volumes of interest (VOI) before and on treatment. For [^18^F]BMS-986192 manually drawn VOIs will also be calculated for liver, kidneys, lungs, spleen and left ventricle of the heart.

(Serious) adverse events

We will pay special interest to all adverse events during the study, in order to obtain information on safety and tolerability of neoadjuvant nivolumab in patients with locally advanced oral cancer who are planned for treatment with curative intent including surgery.

## Secondary study parameters/endpoints

#### Heterogeneity analysis

#### Interpatient, intrapatient and intratumor SUV heterogeneity.

Correlation between both PET scans, and between imaging and response

The correlation between SUV for [^18^F]BMS-986192 and [^18^F]-FDG baseline and on treatment and early response evaluation with [^18^F]-FDG.

Correlation between PET data and Blood/Tissue markers

The correlation between continuous values as SUV and the categorical variables tissue PD-1 and PD-L1 IHC will be assessed for each tumor lesion. Correlation with immuno-monitoring analysis in tumor tissue/lymph nodes and blood, plasma vesicle miRNAs from blood, as well as DNA/RNA profiling in tumor tissue at baseline and at surgery will be assessed.

# STUDY PROCEDURES

The Schedule of assessments (see section [7.19](#_7.19_Schedule_of)) summarizes the study procedures to be performed at each visit. Individual study procedures are described in detail below. It may be necessary to perform these procedures at unscheduled time points if deemed clinically necessary by the investigator. Furthermore, additional evaluations/testing may be deemed necessary for reasons related to subject safety. In some cases, such evaluation/testing may be potentially sensitive in nature (e.g., HIV, Hepatitis C, etc.), and thus local regulations may require that additional informed consent be obtained from the subject. In these cases, such evaluations/testing will be performed in accordance with those regulations.

## Informed Consent

The investigator must obtain documented consent from each potential subject prior to participating in a clinical trial. Consent must be documented by the subject’s dated signature or by the subject’s legally acceptable representative’s dated signature on a consent form along with the dated signature of the person conducting the consent discussion. A copy of the signed and dated consent form should be given to the subject. The initial informed consent form, any subsequent revised written informed consent form and any written information provided to the subject must receive the IRB/ERC’s approval/favorable opinion in advance of use. The subject or his/her legally acceptable representative should be informed in a timely manner if new information becomes available that may be relevant to the subject’s willingness to continue participation in the trial. The communication of this information will be provided and documented via a revised consent form or addendum to the original consent form that captures the subject’s dated signature or by the subject’s legally acceptable representative’s dated signature.

Specifics about a trial and the trial population will be added to the consent form template at the protocol level. The informed consent will adhere to IRB/ERC requirements and applicable laws and regulations.

## Inclusion/exclusion criteria

All inclusion and exclusion criteria will be reviewed by the investigator or qualified designee to ensure that the subject qualifies for the trial.

## Medical history

A medical history will be obtained by the investigator or qualified designee. Medical history will include all active conditions, and any condition diagnosed within the prior 10 years that are considered to be clinically significant by the Investigator.

## Prior medications

The investigator or qualified designee will review prior medication use, including any protocol-specified washout requirement, and record prior medication taken by the subject within 28 days before starting the trial.

## Concomitant medications

The investigator or qualified designee will record medication, if any, taken by the subject during the trial. All medications related to reportable Serious Adverse Events (SAEs) should be recorded as defined in section [8.1](#_AEs,_SAEs_and).

## Disease details

The investigator or qualified designee will obtain prior and current details regarding disease status.

## Assignment of screening number

All consented subjects will be given a unique screening number that will be used to identify the subject for all procedures that occur prior to the PET scans and nivolumab treatment. The screening assignment will start with the term NeoNivo followed by the number of inclusion (e.g. NeoNivo001).

## Adverse event monitoring

The investigator or qualified designee will assess each subject to evaluate for potential new or worsening AEs as specified in the Trial Flow Chart and more frequently if clinically indicated. Adverse experiences will be graded and recorded throughout the study according to NCI CTCAE Version 5.0 Toxicities will be characterized in terms regarding seriousness, causality, toxicity grading, and action taken with regard to trial treatment.

## (Full) physical exam

The investigator or qualified designee will perform a complete physical exam during the screening period and during follow up. Clinically significant abnormal findings should be recorded as medical history. Between screening and surgery, a directed physical exam as clinically indicated will be performed.

## Vital signs

The investigator or qualified designee will take vital signs at screening, prior to the administration of nivolumab and at first follow up visit as specified in the Trial Flow Chart. Vital signs should include temperature, pulse, respiratory rate, weight and blood pressure. Height will be measured at screening only.

## Laboratory procedures/assessments and blood collection

Details regarding specific laboratory procedures/assessments to be performed in this trial are provided below. The total amount of blood to be collected over the course of the trial (from pre-trial to post-trial visits), including approximate blood volumes collected per visit and by sample type per subject will be 328 ml.

For laboratory tests for hematology, chemistry and others, specified in Table 2, 1x7 ml EDTA tube and 1x7 ml Heparin Gel tube will be taken at screening and at follow-up. For WOCBP an additional 1x7 ml serum gel tube will be taken at screening for β-HCG measurement. Laboratory tests for screening should be performed within 14 days prior to the first study procedure.

**Table 2** Laboratory Tests

| **Hematology** | **Chemistry** | **Other** |
| --- | --- | --- |
| Hematocrit | Albumin | Free thyroxine (T4) |
| Hemoglobin | Alkaline phosphatase | Thyroid stimulating hormone (TSH) |
| Platelet count | Alanine aminotransferase (ALT) |  |
| Total WBC | Aspartate aminotransferase (AST) | Blood for correlative studies |
|  | Lactate dehydrogenase (LDH) |  |
|  | Amylase |  |
|  | Lypase |  |
|  | Creatinine |  |
|  | Calcium |  |
|  | Glucose |  |
|  | Phosphorus |  |
|  | Potassium |  |
|  | Sodium |  |
|  | Chloride |  |
|  | Magnesium |  |
|  | Total Bilirubin |  |

Peripheral blood samples for the purpose of immunomonitoring, genomic profiling and plasma vesicle miRNAs will be collected at the following timepoints:

T1 = baseline, before first [^18^F]BMS-986192 PET scan

T2 = 10 days after nivolumab, same day as check-up visit

T3 = 21 days after nivolumab, before second [^18^F]BMS-986192 PET scan

T4 = at follow-up (specified per analysis below).

For immuno-monitoring heparinized blood (4x10ml) will be taken at each of these time points and PBMCs isolated. Follow-up samples will be collected at 3 months after surgery.

For plasma vesicle miRNA analysis EDTA blood (12 ml) blood will be drawn at the same timepoints and at follow-up at 1 and 3 months post-surgery and at progression of disease (in case this occurs after the T4 (6 months) time point).

For genomic analysis, 1x7ml EDTA will be taken at screening for germ line DNA analysis

Total blood collection

Standard of care blood collection: 70ml

Study blood collection: = 258 ml

